### Ethics

This study has been meticulously designed with a strong commitment to ethical standards, ensuring the protection and well-being of all participants. The research protocol has been thoroughly reviewed and approved by the ‘Panagiotis and Aglaia Kyriakou’ Hospital’s Scientific Council, under the Institutional Review Board (IRB) with protocol number 11333, 09th/04-05-2023 (Θ: 9). Additionally, the study has been registered on the clinical trials platform (www.clinicaltrials.gov) under the unique identifier NCT06398912, ensuring transparency and adherence to global research standards.

Participation in this study is entirely voluntary, and informed consent is a central component of the ethical process. Therefore, parents of identified premature infants who meet the inclusion criteria are invited to a detailed one-on-one meeting with the research team, in order to receive comprehensive information, both orally and in writing, regarding the study’s objectives, methodologies, and procedures. This meeting covers all aspects of the intervention and data collection, including the non-invasive nature of the research tools, such as music and EEG, while also addresses any concerns related to selection, participation, withdrawal, confidentiality, and the study timeline, ensuring that parents are fully informed before making a decision.

During this meeting, the voluntary nature of participation is emphasized, with parents being assured that their decision to participate or withdraw at any point will not affect their relationship with the researchers or the medical staff at the Panagiotis & Aglaia Kyriakou Children’s Hospital. They are also informed that in the event of withdrawal, all data associated with the participant will be immediately deleted, ensuring no residual information remains.

Considering the sensitivity of the particular context, and to further protect the participants’ privacy and confidentiality, all collected data are de-identified and pseudonymized at the source (i.e., embeded function of the **nëo™** EEG monitoring unit during the extraction process), with each dataset assigned a unique identification number. Personal identifiers, such as names, are not linked to the data in any study analysis, report, or publication phase, while parents are informed of their right to access the data collected from their infants at any time. Once parents have received all relevant information and have had their questions answered, they are asked to provide written consent, indicating their agreement to participate in the study.

At this point, we should mention that despite its non-invasive nature, the study recognizes potential risks, such as the overstimulation of infants due to sound exposure and stress related to handling. To mitigate these risks, sound levels are closely monitored using a dB dosimeter – as already mentioned – and interventions are scheduled in this way so to ensure adequate rest periods for the infants. It has already been pointed above that the study is conducted in a specially designated, quiet room within the NICU to minimize stress, while moreover, the application of EEG electrodes, a key part of the study, is performed by specialists trained in neonatal care, further reducing the risk of discomfort or stress for the infants. In case of any unforeseen medical complications or adverse reactions, the study protocol includes provisions for the immediate cessation of the intervention and prompt medical evaluation, ensuring the safety of the participants.

#### Results – descriptive statistics.

In terms of the EEG analysis results for this dataset, the descriptive statistics for spectral power in the Delta frequency across different facilitators and conditions are detailed in Table 2 below. The highest mean spectral power was observed during maternal interventions, particularly in the ‘NoteA’ condition (Mean = 1381.3 *μ*V^2^, SD = 1794.5 *μ*V^2^), emphasizing the notable influence of maternal presence in general.

**Table 2 pone.0328211.t002:** Descriptive statistics for spectral power on delta frequency (in *μ*V^2^ for Mean and SD).

Facilitator	Condition	Mean	Standard Deviation	Coefficient of Variation (%)
[name]	NoteA	276.1	269.9	97.7
Father	NoteA	657.1	937.4	142.7
[name]	NoteA	273.6	129.5	47.3
Mother	NoteA	1381.3	1794.5	129.9
Total	NoteA	647.1	1047.2	161.8
[name]	Silence1	92.7	83.4	90
Father	Silence1	161.2	175.8	109.1
[name]	Silence1	339	308.7	91.1
Mother	Silence1	703.1	745.9	106.1
Total	Silence1	324	451.8	139.4
[name]	Silence2	114.8	162.3	141.4
Father	Silence2	148.7	103.3	69.4
[name]	Silence2	225.7	137.3	60.9
Mother	Silence2	218	168.8	77.4
Total	Silence2	176.8	141.6	80.1
[name]	Silence3	94.3	84.6	89.7
Father	Silence3	427.6	785.9	183.8
[name]	Silence3	378.3	538.1	142.2
Mother	Silence3	1020.7	1797.1	176.1
Total	Silence3	480.2	995.9	207.4
[name]	Song	79.1	76.2	96.4
Father	Song	574.2	920.8	160.4
[name]	Song	270.2	231.8	85.8
Mother	Song	213.4	185.7	87
Total	Song	284.2	482.5	169.8

#### Statistical Assumptions Check.

Following the descriptive statistics, and before running the mixed-effects model as planned, assumptions checks were performed by creating a Q-Q plot to assess the normality of residuals and conducting a Breusch-Pagan test for homoscedasticity. The Q-Q plot (Fig 4) indicated that residuals followed an approximately normal distribution, although this approximation was influenced by the presence of a few outliers. Due to the limited sample size available, we chose in this case not to exclude these outliers from the analysis to avoid further reducing the already limited statistical power. Practically, retaining these outliers means our estimates and associated inferences remain conservative, reflecting real-world variability more accurately but potentially inflating error variance slightly. Additionally, the Breusch-Pagan test yielded a p-value of 0.066, suggesting that residual variance remained sufficiently consistent across the fixed effects, thus indicating that the assumption of homoscedasticity holds.

**Fig 4 pone.0328211.g004:**
[figure not shown]
Q-Q Plot of Residuals with a reference point to the female music therapist for the facilitators and the ‘Silence1’ condition for the five intervention conditions.

**Fig 5 pone.0328211.g005:**
[figure not shown]
Interaction Plot of Delta Spectral Power by Condition and Facilitator. This figure illustrates the mean delta spectral power (y-axis) across five experimental conditions – Silence1, NoteA, Silence2, Song, and Silence3 (x-axis) – for the four facilitators ([name], Mother, Father, and [name]). Error bars represent the standard deviation (SD) of individual measurements, highlighting the variability of infants’ responses within each facilitator’s group.

More specifically, we realized that mostly during the ‘NoteA’ condition (as also observed in most of the other conditions), there was a significant increase in Delta Spectral Power for the ‘mother’ facilitator, while surprisingly, the ‘Song’ condition showcased the highest impact particularly for the ‘father’ facilitator. As far as the ‘female music therapist ([name])’ facilitator is concerned, the most stable and lowest Delta Spectral Power across all conditions was observed, indicating a consistent but minimal impact, while the ‘male music therapist ([name])’ facilitator showed moderate variability with minor peaks during the ‘NoteA’ and ‘Song’ conditions. Please note here, that especially for the ‘Song’ condition, the ‘male music therapist ([name])’ facilitator ranked second in impact after the ‘father’ facilitator. To further clarify these specific differences, post-hoc comparisons using the Least Significant Difference (LSD) test were conducted as previously decided, revealing that Delta brain activity was significantly higher with the ‘Mother’ facilitator compared to ‘[name]’ (M = 575.92, *p* = 0.002), ‘[name]’ (M = 409.96, *p* = 0.025), and ‘Father’ (M = 313.55, *p* = 0.085) – although for this latter coming quite close to being significant. Additionally, the ‘NoteA’ condition elicited significantly higher brain activity than the ‘Silence2’ condition (M = 470.26, *p* = 0.022) and showed close trends towards significance when compared to the ‘Silence1’ (M = 323.06, *p* = 0.112) and ‘Song’ conditions (M = 362.86, *p* = 0.075).

#### Secondary Outcomes.

Finally, as already mentioned, in addition to the analysis of Delta spectral power, we also explored the spectral entropy within the Delta frequency band to assess the complexity and predictability of the EEG signals under different facilitators and conditions. The mixed-effects model analysis for spectral entropy revealed once more a significant effect of the ‘facilitator’ parameter on entropy values [F(3, 88) = 2.744, *p* = 0.048], while the spectral entropy across the ‘conditions’ parameter did not exhibit a significant overall effect [F(4, 88) = 0.380, *p* = 0.822]. Especially for the former result, underscoring that the facilitator’s role notably influences the variability and regularity of the EEG signals, we realized that, specifically, the ‘father’ facilitator was associated with the highest mean entropy (M = 0.684, SE = 0.133), while the ‘mother’ facilitator showed the lowest mean entropy (M = 0.558, SE = 0.133) (please see also Fig 6); although pairwise comparisons did not reach statistical significance (in all cases except the close to significance trend of the ‘father’ vs ‘mother’ comparison) after Bonferroni correction (please see Table 4).

**Table 4 pone.0328211.t004:** Pair-wise comparison of the ‘facilitator’ condition after Bonferroni correction.

Comparison	Mean Difference	Standard Error (SE)	p-value
[name] vs. Father	−0.02	0.049	1
[name] vs. [name]	0.063	0.049	1
[name] vs. Mother	0.106	0.049	0.207
Father vs. [name]	0.083	0.049	0.589
Father vs. Mother	0.126	0.049	0.075
[name] vs. Mother	0.043	0.049	1

**Fig 6 pone.0328211.g006:**
[figure not shown]
Mean spectral entropy within the Delta band, showing a significant effect of the ‘facilitator’. The ‘father’ shows the highest mean entropy and the ‘mother’ the lowest.

## Discussion

Although there is emerging evidence that musical interventions can positively influence the neurodevelopment of premature infants, existing studies often suffer from limited control over confounding variables, and a lack of rigorous neuroimaging-based evidence to support the precise neural mechanisms underlying these effects. Against this backdrop, the aim of the present study is to fill these gaps by providing robust data on the effects of a structured singing intervention, specifically focusing on the F0 of the voice and kinship of the music facilitators parameters, on the brain activity of premature infants in a NICU setting. Building upon this foundation, some of the key strengths of the protocol presented here include: (1) the adoption of a single-arm exploratory design that enables detailed within-subject and between-session comparisons; (2) the employment of an advanced neuroimaging technique to precisely monitor and study neural correlates of the intervention; and (3) the consideration of a variety of caregivers – in terms of kinship and voice register – to deeper explore the specific impact of singing on premature infant brain development.

More specifically, the protocol was meticulously designed to ensure a structured framework, while designed as a single-arm exploratory study, allowing for an in-depth exploration of the intervention’s specific impact through both within-subject and between-session comparisons. This design enables the observation of changes in individual participants over time, providing insights into intra-individual variability and the effects of repeated exposure to the intervention. Additionally, between-session analyses will offer a broader understanding of how the intervention might generate consistent patterns across participants, thereby identifying key mechanisms of action. These analyses are crucial for detecting subtle, short-term neurophysiological responses that might be overlooked in larger controlled trials where individual variability can be masked. Thus, the single-arm design is particularly valuable for revealing complex intervention-outcome relationships and generating hypotheses that inform more targeted and rigorous future research. By focusing on individual responses, the study can highlight nuanced effects, identify key factors influencing brain activity, and ultimately provide foundational data to guide subsequent, more expansive studies.

Furthermore, by employing electroencephalography (EEG) and utilizing a custom-made and adapted EEG (pre)processing pipeline, the effects of our live singing intervention on premature infants can be studied in greater detail. This advanced neuroimaging approach allows for a nuanced understanding of how different auditory stimuli influence brain activity in this vulnerable population. As discussed in previous work [30], neuroimaging-guided interventions should be more extensively introduced in the NICU because they can provide real-time insights into the brain’s response to external stimuli, capturing dynamic changes that might not be observable through behavioral measures alone. In this regard, our protocol not only enhances the precision of our study but also contributes to the development of more tailored applications in the future, optimizing music-based interventions to suit the unique neurodevelopmental needs of each infant in the NICU.

Finally, it is important to point out that the study design we decided to implement includes the chosen variety of caregivers to allow us to provide a more comprehensive insight into the role of emotional and social factors evident and embedded in the treatment process of premature infants in real-world situations and environments. For that matter, on the one hand, the inclusion of both parents in the protocol ensures that the study captures potential sex-specific effects, which could be related to differences in voice register or emotional bonding, while, on the other hand, incorporating professional music therapists as facilitators offers a standardized comparison to the former set of caregivers, helping to differentiate the effects of kinship as well as musical and clinical expertise related to the implementation of music-based interventions in this sensitive context. This diversity in caregivers could not only enrich the study’s findings but may also enhance the generalizability of its results, ultimately leading to more comprehensive recommendations for NICU music-based interventions.

Having said the above, the preliminary findings of our study provide intriguing evidence supporting differential effects of parental voices on neonatal brain activity, particularly highlighting the potential influence of the father’s voice. Specifically, the initial EEG analyses suggest that paternal singing elicited notably higher delta spectral power compared to maternal and therapist singing during the lullaby (Song) condition. This preliminary result aligns well with existing literature [103], which suggests that lower-pitched sounds – typically associated with male voices – may uniquely stimulate neural circuits at this developmental stage due to their distinct bioacoustic properties and the specific auditory needs of fetuses – and by extension premature neonates. Moreover, the father’s voice might confer additional familiarity and emotional significance owing to biological kinship. If further analyses confirm these findings, extended paternal involvement may then offer emotional and social stimuli complementary to maternal care, thereby contributing to more robust caregiver-infant bonding dynamics during this sensitive developmental period.

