- *H1*: We hypothesize that when premature newborns are exposed to a live singing intervention provided by their mother (high fundamental frequency – biological kinship) compared to the father (low fundamental frequency – biological kinship) or an unrelated male/female music therapist, they show statistically more visible short-term positive oscillatory differentiations in their brain activity.

- *H0*: We assume that there is no interaction between the fundamental frequency and the kinship profile (mother, father, man, woman) in the infant’s reactions, and that neither the fundamental frequency nor the human profile has a primary effect.

To answer the research question and study its hypotheses, this study will utilize electroencephalography (EEG) to monitor and analyze the brain activity of NICU infants. By comparing EEG patterns across different music delivery conditions of F0 and kinship source (i.e., music facilitators), the findings are expected to provide valuable insights that can be leveraged to enhance neurodevelopmental outcomes in premature infants.

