**Fig 2 pone.0328211.g002:**
[figure not shown]
Study Protocol Flow Chart.

In this design, although the EEG will be the primary tool of data collection and analysis, the rationale for incorporating video data is multifaceted. Firstly, the video recordings will complement the electroencephalogram (EEG) recordings in offering a comprehensive parallel view of the infants’ neural and behavioral responses. Furthermore, the videos will serve as a tool for quality control by ensuring that the prescribed research protocol is uniformly followed by all facilitators, contributing to the scientific integrity of the research. Finally, the videos will allow for a later examination of any synchrony or coordinated interactions between the infant and the facilitator, shedding light on phenotypical – not able to be measured by the EEG – aspects of the intervention.

The live singing intervention will be delivered by four different profiles of individuals-facilitators: a male music therapist, a female music therapist, the mother, and the father of the newborn. During the delivery of the intervention (explained in more detail below), there will be five ‘conditions’ measured: Silence1 (180 seconds), Note A (60 seconds), Silence2 (180 seconds), Song (90 seconds) and Silence3 (180 seconds).

It is important to note that the study protocol will be conducted in a dedicated room, largely isolated from the ambient noise typically found in the rest of the NICU. This aspect of the study design is crucial for two main reasons:

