Firstly, it will ensure the comfort and safety of the participating newborns. All actions taken in the context of the NICU require adherence to the recommended standards for the NICU sound environment. Therefore, the importance of a well-managed acoustic environment in reducing stress and discomfort for our participating infants is of paramount importance. Such a consideration has been consistently highlighted both for clinical and research settings alike [32] and a sound-controlled room within the NICU seems to be the only viable option for achieving the necessary level of sound management for our participants, without disrupting other clinical operations. More specifically, in the NICU context, when considering the operational sound as outlined by White, Smith, Shepley, et al. [31], the combination of continuous background sound and operational sound should not exceed an hourly L_eq_ of 45 dB and an hourly L_10_ of 50 dB, both A-weighted slow response, with transient sounds or L_max_ not exceeding 65 dB. Our study, with sound exposure lasting less than 3 minutes per hour, will strictly adhere to these guidelines. However, the transient nature of singing, distinct from the continuous and better-controlled sound pressure levels typically found in continuous speech, might lead to brief instances where we slightly exceed these thresholds by about 15 dB. According to evidence, even professional singers, and more so untrained individuals like the parents participating in our study, are not able to produce transient peak Sound Pressure Levels (SPLs) below 78–79 dB when singing softly [70]. However, it has been noted that in environments with lower ambient noise, humans can more easily maintain a soft vocal output because the reduced background sound allows for greater control and minimizes the need to compensate with higher volume [71]. Therefore, we believe that a dedicated room will significantly aid in ensuring the correct application and viability of the aforementioned recommendations – by providing an acoustically controlled setting that minimizes ambient noise and facilitates softer singing performance – as compared to the open NICU floor, thus preventing the intervention from inadvertently exceeding the recommended soundscape limits.

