Most importantly, from a clinical perspective, neonatal studies must be designed to target effects that will lead to meaningful changes in patient care. Reviews in neonatal contexts (e.g., [88]) stress that interventions in this vulnerable population should only be implemented if they can yield substantial improvements in clinical outcomes, while ethical considerations – such as minimizing exposure to potentially stressful interventions – further support the choice of a conservative MESI. Particularly, Akoglu [89] emphasizes that effect size selection should reflect the minimal clinically important difference. In result, after reviewing the relevant clinical and methodological literature and consulting with field experts involved in our research protocol, the aforementioned MESI threshold was deemed appropriate, ensuring that our power analysis is finely tuned to detect only those effects that hold substantial clinical significance, thereby safeguarding patient care by focusing on differences that are both statistically robust and practically meaningful.

With our designated MESI – as explained above – and by setting alpha at 0.05 and power at 0.80, we conducted an a priori power analysis using G*Power 3.0 for an ANOVA: Repeated measures, within factors design. This analysis incorporated our 5 repeated measurement conditions (Silence1, NoteA, Silence2, Song, Silence3) to account for the experimental structure of the study, with a correlation among repeated measures and a non-sphericity correction to reflect realistic assumptions regarding the correlations and potential sphericity violations among repeated measures.

The power analysis indicated that 14 participants would be sufficient to achieve the desired power level of 80% to detect the specified effect size, with an actual power of 83% (Table 1). We should clarify that in this case we chose G*Power 3.0 as this is more tailored to adjustments specific to repeated-measures designs, such as accounting for non-sphericity and correlations among repeated measures.

**Table 1 pone.0328211.t001:** Power analysis table.

Effect Size Specification	G*Power 3.0 – F tests – ANOVA: Repeated measures, within factors	
**Tool**	**G*Power 3.1.9.7**	
		
**Analysis:**	A priori: Compute required sample size	
**Input:**	Effect size f(V)	0.35
	α err prob	0.05
	Power (1-β err prob)	0.80
	Number of groups	1
	Number of measurements	5
	Corr among rep measures	0.5
	Nonsphericity correction ε	0.75

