Finally, to ensure the best possible implementation of the intervention – particularly regarding the singing process – all parents of participants who meet the study’s inclusion criteria will receive 30 minutes of training before the actual intervention. This training will be conducted by a member of the research team who is a professional musician, singer, and music therapist. This pre-intervention session aims to equip parents with the necessary skills and understanding to enhance the intervention’s effectiveness, ensuring close consistency among the different facilitators. Additionally, the training session is designed to provide a calming influence on the parents, which can reduce stress and anxiety for both the infants and their caregivers during the delivery of the intervention. We believe that this pre-intervention training will empower parents as active participants in their child’s care, improving adherence and contributing to a more supportive and therapeutic environment throughout our study in the NICU.

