### Outcomes and statistical analysis

To rigorously evaluate the effects of our live singing intervention, we decided to employ a series of advanced statistical methods tailored to the specificities of the study design and data characteristics. The complete analysis focused on the EEG-based outcome measures, with an emphasis on Spectral Power (primary outcome) and Spectral Entropy (secondary outcome), across the Delta frequency band.

Special attention was given to the Delta frequency band as it is widely recognized for its relevance in neonatal brain activity [99–100]. The Delta frequency band, typically ranging from 0.5 to 4 Hz, is the slowest of the EEG frequency bands and is a critical marker of brain maturation. Higher absolute power in the delta frequency band has been associated with more favorable long-term neurodevelopmental outcomes, reflecting the progression of underlying neural processes during early development [99]. Given its prominence in this context, we believe that the Delta frequency band can be an essential marker for assessing the impact of sound and music on the neurophysiological state of our participants, providing in result critical insights into how these infants process auditory stimuli and the extent to which our intervention influences brain activity patterns.

More specifically to the design of our statistical analysis process and given the study’s repeated measures design and the nested data structure (with multiple observations per infant), a mixed-effects model was decided to be employed to analyze first the Delta Spectral Power, allowing for the inclusion of both fixed effects (conditions and facilitators) and random effects (variability across individual infants), while also meticulously fitting the model to account for the inter-individual variability after isolating the impact of the different intervention conditions and facilitator profiles.

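### The Discussion says the design separates kinship from musical and clinical expertise, but the two coincide in all four facilitators

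*Protocol article*

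**What the plan says.** Methods, Study design, names the four facilitators as "a male music therapist, a female music therapist, the mother, and the father of the newborn". The same section, on sound levels, refers to "untrained individuals like the parents participating in our study". The Intervention section adds that parents "will receive 30 minutes of training before the actual intervention"; it describes this session for parents only.

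H1, under Study objectives, gives mother and father biological kinship and sets the mother against the father or "an unrelated male/female music therapist". Kinship is also part of the primary research question and of H0.

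The mixed model under Outcomes and statistical analysis has "fixed effects (conditions and facilitators) and random effects (variability across individual infants". Facilitator is a single factor, with no separate term for training or profession.

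The Discussion then says that "incorporating professional music therapists as facilitators offers a standardized comparison to the former set of caregivers", and gives as the benefit "helping to differentiate the effects of kinship as well as musical and clinical expertise". Challenges and limitations does not mention that kinship and expertise coincide.

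**The concern.** The Discussion names two effects, kinship and expertise, and says the choice of singers helps to tell them apart. That needs at least one singer who is related and professional, or unrelated and lay. The plan has neither.

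Kinship is in the primary question and in both hypotheses, so this bears on what the study can conclude. The article itself gives reasons why the parent-therapist line may carry more than kinship:

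- Study design says that singing softly is harder for untrained people than for professionals, so loudness could differ along this line.
- The Introduction says that the voice of a non-related caregiver may be less familiar to the infant.
- Challenges and limitations says that the parents' emotional state could affect delivery.

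A reader who trusts the Discussion would think the design had dealt with expertise, and could read a mother-therapist difference as kinship.

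**Working it through.** **1. The plan's own design figure.** Table 1 gives f = 0.35, alpha 0.05, 5 measurements, correlation 0.5 and epsilon 0.75. With N = 14:

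- Noncentrality = 0.35² × 14 × 5 × 0.75 / (1 − 0.5) = 12.8625.
- Degrees of freedom = 4 × 0.75 = 3 and 13 × 4 × 0.75 = 39; critical F = 2.845.
- Power = 0.827, against 0.83 stated. N = 13 gives 0.792.

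So the stated 14 reproduces. It concerns the five conditions, not the facilitators, and nothing below depends on it.

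**2. The four cells.** Coded from Study design, Study objectives, Intervention and Discussion:

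| Facilitator | Sex (female = 1) | Kinship | Expertise |
|---|---|---|---|
| Mother | 1 | 1 | 0 |
| Father | 0 | 1 | 0 |
| Male therapist | 0 | 0 | 1 |
| Female therapist | 1 | 0 | 1 |

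Expertise = 1 − kinship in every row, so their correlation is −1.

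**3. Rank.**

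- Intercept, sex, kinship: 3 columns, rank 3.
- Adding expertise: 4 columns, rank 3.
- Intercept, sex, kinship, sex × kinship: 4 columns, rank 4.
- Adding expertise: 5 columns, rank 4.

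Sex, kinship and their interaction use all three facilitator degrees of freedom.

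**4. More infants.** For 14 × 4 × 5 = 280 observations with infant and condition terms, the matrix has 21 columns with expertise. Its rank is 20 with that column and 20 without it. Further infants repeat the same four rows. Adding one unrelated lay singer would bring the matrix of intercept, sex, kinship and expertise to full rank 4; this only shows where the gap lies.

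**5. What each comparison estimates.** Let the additive facilitator effects be S (sex/F0), K (kinship) and E (expertise).

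- Mother − father = S.
- Female − male therapist = S.
- Mother − female therapist = K − E.
- Mother − male therapist = S + K − E.

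K never appears without −E. A sex × kinship term changes some of these expressions but does not release K from E.

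**6. An example from the preliminary results.** From Table 3, mother minus female therapist is 707.362 − 131.442 = 575.92 µV², the difference reported from the LSD test. (Therapist names are removed; the Results describe the female therapist as the lowest.) On the additive model this fits K = 575.92 with E = 0, or K = 0 with E = −575.92, or any other pair with K − E = 575.92. The data cannot favour one pair over another.

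**The case against.** The strongest reply is that this is one clause in a Discussion. Expertise is not in the research question, the hypotheses or the model, so no planned test depends on separating it. The clause speaks only of helping, and could mean that therapists supply a contrast to parents. The plan also fixes singing distance, note and song and trains the parents, which narrows the skill gap. Study objectives already concedes weaker causal interpretation.

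Some of this stands. The point concerns a claim and an interpretation, not a faulty test. But the clause names expertise alongside kinship as effects to be differentiated. Thirty minutes of training does not make a parent a professional musician or clinician. The concession in Study objectives is tied to the lack of a comparison group. A parent who happened to be a musician could break the aliasing by chance, but the article plans for no such case.

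Four stronger readings are tempting and are not supported:

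- **That the article reports a pooled parent-therapist difference as kinship.** It does not. The post-hoc tests are pairwise, and the Discussion invokes kinship only for the father, in hedged terms. The pooled figure can be formed from Table 3, (707.362 + 393.818)/2 − (131.442 + 297.398)/2 = 336.17 µV², but it is neither planned nor reported.
- **That H1 should become parents versus therapists.** H1 sets the mother against each other facilitator. Pooling the parents would replace it with another hypothesis and lose mother versus father.
- **That the gap between the therapists measures voice-to-voice variation missing from the standard errors.** The gap is 297.398 − 131.442 = 165.96 µV². It contains the sex/F0 effect and sampling error. With 25 observations per facilitator (5 infants × 5 conditions) and the article's scale parameter, its SE is √(2 × 404,271/25) = 179.8. Subtracting sampling error gives a between-voice variance of 165.96²/2 − 404,271/25 = 13,771 − 16,171, which is below zero. No inflation can be estimated from these data.
- **That the same two people sing to every infant throughout.** The singular wording and the single therapist labels in the results suggest it, but the article does not state it for the full study.

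**Conclusion.** The Discussion claims a property that the design lacks. Kinship and professional expertise are fully aliased across the four facilitators, at any number of infants and under any analysis of these cells. A parent-versus-therapist difference, including mother versus either therapist in H1, cannot be attributed to kinship rather than training, and familiarity lies along the same line.

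The damage is confined to those comparisons. Mother versus father is not aliased with professional training. Male versus female therapist is not aliased with kinship or professional status, but rests on one voice per sex.

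The conclusion is structural and has no size in µV². It assumes only that parents are lay singers and therapists professional, as the article describes them. It does not invalidate the study, but it limits the answer to the kinship part of the primary question.

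**What to change.** - In the Discussion, delete the claim that the choice of facilitators differentiates kinship from expertise.
- Leave H1's comparisons as they are. State with the hypotheses and in the results that every parent-versus-therapist comparison is a joint effect of kinship, training and familiarity.
- Add the aliasing to Challenges and limitations.
- Say whether the same two therapists serve all infants. If so, state that inference is conditional on those two voices.
- Note that mother versus father is free of aliasing with professional training. Note that male versus female therapist is free of aliasing with kinship and professional status but has one voice per sex.

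The cost is wording only: no new singers, sessions or infants. The price is a narrower kinship conclusion. The article describes the study as still in progress, so the change can precede the final analysis.
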